**Methods:**

This is a 2-arm, parallel-group randomized controlled trial. A total of 196 community-dwelling older adults 60 years and older will be randomized to either the intervention group, comprising a digital strength and balance program (KOKU) alongside standard care (strength and balance exercise advice and a falls prevention leaflet), or to a control group, receiving standard care only. Participants receiving the intervention will be asked to exercise 3 times per week following the tailored and progressive program. Randomization will take place after recruitment and baseline data collection. The trial’s primary outcome measure is balance function (Berg Balance Score) at 12 weeks post randomization. Secondary trial outcomes include lower limb strength, health care utilization and health-related quality of life, self-reported concerns about falling, self-reported physical activity, falls risk, pain, mood, fatigue, self-reported falls, and acceptability and usability of the KOKU program. Intention-to-treat analysis and a cost-effectiveness analysis will be employed for trial data analysis. Qualitative interviews and focus groups will be undertaken with around 10 care providers and 13 participants to further understand views of the intervention and trial processes.

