### Randomization and Blinding

Randomization will be performed using Research Electronic Data Capture (REDCap V 14.0.31 [26]) randomization module to allocate older adult participants in a 1:1 ratio to either the intervention or control group. Random permuted blocks of various sizes will be used to produce similar group sizes and preserve allocation concealment. The allocation sequence will be computer-generated and uploaded into the REDCap system by a researcher who is not involved in enrolling or assigning participants to groups.

Responsibility for enrolling participants into the trial lies with the principal investigator and staff at the sites. Allocation concealment will be ensured, as the system will not release the allocation until the participant has been randomized by a researcher not involved in recruitment, after baseline assessments have been taken. Given the nature of the trial, researchers completing data collection and participants will not be blinded. The researcher undertaking data analyses will be blinded to the intervention and control groups to minimize bias.

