### Outcomes

At baseline, a bespoke questionnaire will capture past medical history (including fractures), medication, comorbidities, self-reported level of vision, and demographic data (age, gender, ethnicity, and socioeconomic status). Outcome data will be collected by trained researchers from all participants at baseline, 6 weeks, and at the end of the 12-week period (Table 1).

**Table 1. T1:** KOKU^a^ trial schedule of enrollment, interventions, and assessments.

Timepoint	Prescreening	Enrolment/allocation	Study period postallocation			
			Baseline	Week 6	Week 12	Week 24
Recruitment—research team						
Identify potential care providers for study	✓					
Familiarize care providers with research project	✓					
Recruitment—care providers						
Identify potential study participants	✓					
Patient enrollment						
Eligibility screen	✓	✓				
Informed consent		✓				
Training to use KOKU		✓				
Interview/focus group					✓	
Care provider staff enrollment						
Eligibility screen		✓				
Informed consent		✓				
Training to use KOKU		✓				
Interview/focus group					✓	
Allocation—Interventions						
KOKU			✓	✓	✓	
OEP^b^ leaflet and falls prevention leaflet			✓	✓	✓	
Assessments						
BBS^c^			✓	✓	✓	
5StS^d^			✓	✓	✓	
Health questionnaires^e^				✓	✓	
Adverse events			✓	✓	✓	
Usability/acceptability questionnaires^f^					✓	
Daily falls calendar follow-up			✓	✓	✓	✓

a KOKU: Keep-On-Keep-Up.

b OEP: Otago Exercise Programme.

c BBS: Berg Balance Scale.

d 5StS: Five Times Sit-to-Stand chair test.

e Health questionnaires include 5-item Geriatric Depression Scale, Physical Activity Scale for the Elderly, Short Falls Efficacy Scale-International, Assessment of Falls Risk tool, and EQ-5D-5L.

f Usability/acceptability questionnaires include the System Usability Scale, the Short Version of the User Experience Questionnaire, and the theoretical framework for acceptability.

The primary outcome measure is balance function, as measured by the validated Berg Balance Scale (BBS) [23]. The test involves 14 assessments of static and dynamic balance and is useful in predicting the risk of falls and indicating an individual’s ability to mobilize and carry out activities of daily living.

Secondary outcomes measured at 6 and 12 weeks will be measured by the following assessments:

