### Statistical Analysis

All statistical analyses will be performed using Stata (StataCorp) or SPSS (version 28, IBM Corp; 2021).

Baseline demographic and clinical characteristics will be summarized by trial arm using means and SD, or median and interquartile ranges for continuous variables, as appropriate, and frequencies with percentages for categorical variables.

The primary analysis will be conducted following the intention-to-treat (ITT) principle, including all participants providing evaluable outcome data irrespective of their engagement with the KOKU program or control intervention.

BBS will be analyzed using a mixed model for repeated measures (MMRM). The model will include the fixed effects of trial arm (ie, KOKU and control), time point (ie, 6 and 12 wk), and the fixed covariate of baseline scores, as well as the interactions of all fixed terms by time point, ensuring the effects are permitted to vary for each of the 2 time points. An unstructured covariance matrix will be used, and the model will be fitted using restricted maximum likelihood (RML) estimation. The primary comparison of interest is between group differences at 12 weeks. Results will be presented as regression coefficients with 95% CIs. Continuous secondary outcomes will be analyzed using a similar framework to the primary outcome.

The rate of falls will be analyzed using a parametric model for count data (eg, Poisson or negative binomial), adjusting for baseline values. The appropriate model will be chosen depending on the distribution of this variable. The incident rate ratio will be presented with a 95% CI.

All the models will be adjusted for baseline values. Thus, to minimize data loss, simple mean imputation (across the randomized groups) of the corresponding outcome data will be used. MMRM models are likelihood-based and therefore consistent with the missing-at-random assumption. Sensitivity analyses to assess the robustness of the MAR assumption will be performed for the primary outcome.

Quantitative data will be managed using REDCap [26], a secure, web-based software platform designed to support data capture for research studies, providing (1) an intuitive interface for validated data capture; (2) audit trails for tracking data manipulation and export procedures; (3) automated export procedures for seamless data downloads to common statistical packages; and (4) procedures for data integration and interoperability with external sources.

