### Strengths and Limitations

This study has several strengths. Firstly, it employs an RCT design, minimizing bias and allowing for robust comparisons between the intervention and control groups. Secondly, by using the BBS as the primary outcome measure, the study employs a well-validated and clinically relevant tool to assess balance changes. Balance is widely used as a proxy for falls risk due to its being a key risk factor for falls. As a modifiable risk factor, physical interventions that target balance can directly reduce falls risk. Many falls prevention guidelines recommend balance training with improvements in balance considered a marker of intervention success [7]. Thirdly, the trial incorporates an economic evaluation, which is important for informing policymakers and health care providers about the cost-effectiveness of digital interventions, particularly those tested in real-world conditions. Additionally, by utilizing an intention-to-treat analysis, the study findings will reflect real-life effectiveness in practice.

Despite its strengths, the study has several limitations. In exercise studies, it is very difficult to blind participants or assessors, which can lead to bias. Furthermore, although unlikely, it is possible that participants in the intervention group could share information so that those in the control group have access to the intervention given that some participants were recruited from the same care providers. In addition, larger, fully powered studies are also needed to investigate the clinical and cost-effectiveness of the KOKU intervention with a primary outcome of fall rates.

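### The falls model could also adjust for baseline Berg Balance Scale score: a small, nearly free gain in precision, not a correction of bias

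*Protocol article*

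**What the plan says.** Falls are a secondary outcome. The Methods part of the abstract lists them among "falls risk, pain, mood, fatigue, self-reported falls, and acceptability and usability of the KOKU program".

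The Statistical Analysis section specifies the falls model in three sentences. The first is "The rate of falls will be analyzed using a parametric model for count data (eg, Poisson or negative binomial), adjusting for baseline values". The second leaves the choice of count model to the distribution of the data. The third is "The incident rate ratio will be presented with a 95% CI". A general rule follows: "All the models will be adjusted for baseline values". The next sentence deals with missing baselines by mean imputation of the matching outcome. The section names no other covariate for falls.

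Two other places bear on the choice of covariate. Under Outcomes, "Outcome data will be collected by trained researchers from all participants at baseline, 6 weeks, and at the end of the 12-week period", and Table 1 schedules the BBS at baseline. Under Strengths and Limitations, the article justifies its primary outcome thus: "Balance is widely used as a proxy for falls risk due to its being a key risk factor for falls".

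On allocation, the Randomization and Blinding section describes a "randomization module to allocate older adult participants in a 1:1 ratio to either the intervention or control group", with permuted blocks and no stated stratification factor. The allocation is released only once "the participant has been randomized by a researcher not involved in recruitment, after baseline assessments have been taken".

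**The concern.** The article presents balance as a principal driver of falls and measures it in everyone before randomization. The falls model as stated does not use it. The phrase about baseline values, read with the imputation sentence and with the use of baseline scores in the BBS model, points to each outcome's own baseline. Where the article wants further covariates it lists them, as in the Economic Analysis section (sex, age, ethnicity, marital status, socioeconomic status and baseline utility). The falls sentence lists none.

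The stake is precision. The trial was sized for the BBS, and the article itself says that larger studies powered for fall rates are still needed. A prognostic baseline covariate that is already collected could narrow the interval around the rate ratio. It would also make the estimate less dependent on how balance happened to fall between the arms. If an imbalance shows up and BBS is added only then, the choice will look data-driven.

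**Working it through.** **Inputs from the article.** BBS SD 14, correlation 0.7, difference 5 points, 90% power, 5% significance (taken as two-sided) and 13% attrition (Sample Size); 102 and 100 randomized (Results).

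**Inputs assumed.** The fall rate, the overdispersion and the slope of fall rate on BBS are not in the article. Ranges are used below. The planning SD of 14 is taken as the baseline SD.

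**1. The plan's own figure.** Adjusted SD = 14 × √(1 − 0.7²) = 9.998. The two-means formula gives 85 per arm; 85 / (1 − 0.13) = 97.7, so 98 per arm and 196 in total. The stated sample size reproduces. It concerns the BBS and does not depend on the falls model.

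**2. Size of a chance BBS difference.** SE = 14 × √(1/102 + 1/100) = 1.97 points, which is 1.97/14 = 0.14 SD. The 0.14 is set by the sample size, whatever the SD.

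**3. Bias and type I error.** Trials of 202 were simulated with no treatment effect, about 0.5 falls per person over 24 weeks, overdispersion 0.8, and a binary fall history in both models (about 1,000 runs per row). The slope is the change in log fall rate per SD of BBS. Each pair is without / with baseline BBS.

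| Slope | Mean log rate ratio | Type I error | Mean model SE | Empirical SE |
|---|---|---|---|---|
| 0.2 | −0.003 / −0.005 | 0.055 / 0.056 | 0.237 / 0.236 | 0.238 / 0.238 |
| 0.4 | 0.010 / 0.012 | 0.041 / 0.032 | 0.245 / 0.239 | 0.236 / 0.225 |
| 0.6 | −0.012 / −0.010 | 0.071 / 0.068 | 0.257 / 0.242 | 0.281 / 0.254 |

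Both models are centred near zero. The Monte Carlo SE of the type I error is about 0.007. At slope 0.6 both models sit above 5% by much the same amount, so the excess cannot be put down to leaving BBS out.

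**4. Precision with fall history in the model.** Variance reduction = 1 − (SE with / SE without)².
- Model SE: 1 − (0.236/0.237)² = 1%; 1 − (0.239/0.245)² = 5%; 1 − (0.242/0.257)² = 11%.
- Empirical SE: 0%; 1 − (0.225/0.236)² = 9%; 1 − (0.254/0.281)² = 18%.

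**5. Precision without fall history.** A second simulation used 1,500 trials per setting, a true rate ratio of 0.75, dispersion 1, mean falls of 0.3 to 0.8 and log-rate slopes of 0.02 to 0.04 per BBS point (0.28 to 0.56 per SD of 14). The ratio of unadjusted to adjusted variance was 1.02 to 1.19. That is a reduction of 1 − 1/1.02 = 2% to 1 − 1/1.19 = 16%.

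**6. Sensitivity to a realised imbalance.** In the second simulation the unadjusted log rate ratio moved by 0.019 to 0.038 per BBS point of imbalance, and the adjusted one by about zero.
- 2 points (about 1 SE): 0.038 to 0.076 on the log scale, so an arm that starts better by chance shows a rate ratio about 4% to 7% lower. Against a model SE of about 0.24 this is 0.16 to 0.32 of an SE.
- 2 SE (3.94 points, exceeded in about 5% of trials): 0.075 to 0.150, or about 7% to 14%.

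**The case against.** A reader might infer that a chance difference in baseline balance would be mistaken for an effect of the intervention. The documents do not support that. Allocation is random and follows the baseline assessments, so such a difference is random error, and the planned 95% CI already allows for it. Step 3 agrees. The shift in step 6 is conditional on one realised allocation and is well within the interval in ordinary cases. This part of the objection stands in full.

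A reader might also infer that the article shuts BBS out of the falls model, or ranks it as the strongest predictor measured. It does neither. It names no variable and gives no closed list, and it calls balance a key risk factor, not the strongest. The Outcomes section names other predictors, including a fall in the previous year, number of medications, pain and fatigue. A journal article commonly leaves the covariate list to the full protocol or SAP, which is not shown and may already include BBS. So nothing in the article is contradicted, and the absence of a list is not itself a fault.

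The gain is also modest, rests on assumed inputs and concerns a secondary outcome. Fall history, where available, absorbs part of what BBS would explain.

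What remains is narrower. The falls sentence as stated does not use a named prognostic measure that is already collected on everyone, and using it costs almost nothing. BBS is also the safer covariate to rely on. The fall calendars run forward from baseline, and the fall-history item belongs to the health questionnaires, which Table 1 shows at weeks 6 and 12 only although the Outcomes text says outcome data are collected at baseline.

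**Conclusion.** This is a minor improvement and not an error in the plan. Leaving baseline BBS out of the falls model does not bias the rate ratio or raise the false-positive rate. It forgoes some precision: between nothing and just under a fifth of the variance of the log rate ratio across the assumed settings, and about 1% to 11%, by the model's own SE, with fall history also adjusted for. It also leaves the estimate open to a chance BBS imbalance with an SE of about 1.97 points. These figures rest on assumed slopes of 0.2 to 0.6 per SD, 0.3 to 0.8 falls per person, dispersion of 0.8 to 1, and a baseline SD of 14. A weaker relation between BBS and falls in this sample would bring the gain close to zero.

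**What to change.** In the falls sentence of the Statistical Analysis section, name the covariates: baseline BBS as a continuous term, plus any fall history recorded before randomization. Use only the baseline BBS, since the later scores can be affected by treatment. Fix this before the falls data are analyzed. If the SAP already lists baseline BBS for falls, no change is needed.

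The cost is one sentence and one degree of freedom, with no new data. Any missing baseline BBS can take the baseline mean imputation already planned. With a log link and no effect modification the rate ratio is collapsible, so adding the covariate does not change what is being estimated. The sample size is unaffected.

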### Economic Analysis

The primary objective of the economic analysis is to assess the incremental cost-effectiveness of the KOKU program compared with usual care. A cost-effectiveness analysis (CEA) will be conducted alongside the trial from the NHS perspective, excluding patient-incurred costs. The base-case CEA will adopt a 12-week time horizon, consistent with the trial follow-up period.

Health care resource–use data collected during the telephone follow-ups of participants who report a fall will be combined with relevant unit cost data for the financial year 2023 to 2024 to calculate the total costs incurred over the study period. Unit costs will be obtained from available UK health care reference sources. For primary care, the latest Personal Social Services Research Unit reference costs will be used, while for secondary care, costs will be sourced from the latest national reference cost schedule.

Quality-adjusted life years (QALYs) will be calculated based on EQ-5D-5L utility values using the area-under-the-curve method, assuming linear extrapolation of utility between time points. EQ-5D-5L will be scored using the appropriate tariff as recommended by the National Institute for Health and Care Excellence at the time of data collection. Multiple imputation techniques will be used to handle missing data in the main analysis, with the number of imputations determined by the extent of missing data. Regression analysis will estimate incremental costs and QALYs between the intervention and control groups, adjusting for baseline covariates including sex, age, ethnicity, marital status, socioeconomic status, and baseline utility score. Model selection (such as ordinary least squares/general linear models) will be based on goodness-of-fit statistics and diagnostic tests for model specification. Incremental net-monetary benefit will be calculated using a willingness-to-pay threshold of £20,000 (~$26,900) per QALY. Cost-effectiveness acceptability curves will be produced to show the probability of cost-effectiveness across a range of thresholds.

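### As written, the missing-data sentence mean-imputes outcome data across arms and contradicts the MMRM under MAR; it should be limited to missing baseline values

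*Protocol article*

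**What the plan says.** All references are to the protocol article. Four statements in Statistical Analysis bear on missing data:

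- The lead-in: "All the models will be adjusted for baseline values".
- The imputation rule, joined to the lead-in by *thus* and justified as a way to limit the loss of data: "simple mean imputation (across the randomized groups) of the corresponding outcome data will be used".
- The next sentence: "MMRM models are likelihood-based and therefore consistent with the missing-at-random assumption".
- The one after that: "Sensitivity analyses to assess the robustness of the MAR assumption will be performed for the primary outcome".

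The same section defines the primary analysis set as "including all participants providing evaluable outcome data irrespective of their engagement with the KOKU program or control intervention". It specifies the MMRM with "time point (ie, 6 and 12 wk), and the fixed covariate of baseline scores", so baseline is a covariate and only the two follow-up visits are responses. Randomization and Blinding places allocation "after baseline assessments have been taken".

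**The concern.** The rule names outcome data and does not say baseline. It follows a sentence about all the models, so on its face it covers the primary MMRM, the continuous secondary outcomes and the fall-rate model.

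If missing 6- and 12-week scores were filled with one pooled mean, people lost from either arm would receive the same value whatever their baseline. The MMRM would have no missing responses left to handle under MAR, and the MAR sensitivity analyses would have nothing to test. The rule and the two sentences after it cannot all be carried out.

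At stake is the primary estimate. Giving both arms' missing participants a common value pulls the arms together. If dropout is unequal and related to baseline, it can also create a difference where none exists. For fall counts, a pooled mean is generally not an integer and does not suit a Poisson or negative binomial model.

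The literal reading is a real risk. Baseline is assessed before randomization, so missing baseline balance scores should be rare, while the missingness the plan does quantify is 13% attrition (Sample Size). A rule meant to limit data loss is easily taken to address that attrition.

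**Working it through.** **Inputs from Sample Size:** SD 14, baseline to follow-up correlation 0.7, difference 5, power 90%, significance level 5% (taken as two-sided), attrition 13%, 98 per arm.

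**1. The plan's own figure.**
- Baseline-adjusted SD = 14 × √(1 − 0.7²) = 9.998.
- n per arm = 2 × (1.960 + 1.282)² × 9.998² / 5² = 84.02, so 85.
- Inflated: 85 / (1 − 0.13) = 97.7, so 98 per arm and 196 in total. This matches the plan.

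**2. Expected shrinkage if follow-up is imputed.** With a fraction m missing at random in each arm and every gap filled with the same pooled mean, the arm difference becomes (1 − m) × effect = 0.87 × 5 = 4.35.

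**3. Simulation.** 8,000 trials per scenario, 98 per arm, normal scores with baseline mean 40. A 12-week ANCOVA stands in for the MMRM contrast. Three analyses were compared: no imputation; missing 12-week outcomes set to the pooled observed mean; and observed outcomes with missing baseline covariates set to the pooled baseline mean.

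Not in the document, so assumed: 5% missing baseline; unequal dropout of 6% and 20%; and, in the baseline-dependent rows, dropout log-odds rising by 0.8 for each SD of lower baseline, with the listed rates holding at the mean baseline.

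Cells show estimate / coverage / rejection rate.

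| True effect; dropout | No imputation | Outcome imputed | Baseline only imputed |
|---|---|---|---|
| 5; 13%/13%, random | 5.01 / 94.9% / 90.2% | 4.37 / 92.8% / 86.5% | 5.02 / 95.1% / 88.8% |
| 5; 6%/20%, random | 5.01 / 95.0% / 89.8% | 4.33 / 92.6% / 85.9% | 5.01 / 95.2% / 88.6% |
| 5; 13%/13%, baseline-dependent | 5.00 / 94.6% / 88.6% | 4.22 / 91.8% / 82.5% | 5.00 / 94.7% / 87.5% |
| 0; 13%/13%, random | 0.02 / 94.8% / 5.2% | 0.02 / 95.0% / 5.1% | 0.03 / 94.8% / 5.2% |
| 0; 6%/20%, baseline-dependent | 0.02 / 94.6% / 5.4% | 0.86 / 90.2% / 9.8% | 0.07 / 94.6% / 5.4% |

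The Monte Carlo error of a 95% coverage figure is √(0.95 × 0.05 / 8,000) = 0.24 percentage points.

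With 13% missing baseline (also assumed), 13% random dropout and a true effect of 5, baseline-only imputation gives 4.96, coverage 94.9% and power 85.9%. No imputation in the same run also gives 4.96, so this is loss of precision, not bias.

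**4. Where the coverage loss comes from.** In the first row with outcomes imputed, the model SE is 1.419 and the empirical SE 1.413, so the SE is right for that estimator. The bias is 5 − 4.365 = 0.635, or 0.635 / 1.419 = 0.45 SE. A correct SE with that bias gives coverage Φ(1.97 + 0.45) − Φ(−1.97 + 0.45) ≈ 0.93, which accounts for the simulated 92.8%. The SE is smaller only in comparison with the analysis without imputation (1.419 against 1.534, about 7.5%).

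**5. The spurious difference in the last row.** Participants with low baseline drop out and are given the mean of those who stayed, which is higher than they would be expected to score. The arm with more dropout gains more from this, so the 0.86 points favour that arm.

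**The case against.** The strongest reply is that the sentence was never meant for follow-up data, and the text supports this. The rule is drawn as a consequence of baseline adjustment: a participant without the covariate would fall out of the model. Pooling over arms is the usual device for a missing baseline covariate in a randomized trial. The analysis set is limited to people with evaluable outcomes, a limit that would do nothing if outcomes were filled in. A reading that empties the next two sentences is probably not the intended one. Missing baseline values are also plausible for the questionnaire outcomes, even if rare for the balance score.

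This stands as an account of intent. A reader might infer that the trial will fill missing follow-up balance scores with a pooled mean; the document does not establish that. What remains is that the printed rule names the wrong data. An unseen SAP may state it correctly, but this is a rule stated wrongly here, not a detail left out.

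Three further inferences should be resisted:
- **That the literal rule understates the standard error.** Its SE matches its own sampling variability; the coverage loss is mainly bias.
- **That it inflates type I error in general.** With equal random dropout at the plan's 13%, it only attenuates the effect, and rejection under the null stays at 5.1%. The 9.8% needs dropout patterns that the document does not give.
- **That it clashes with Economic Analysis, where** "Multiple imputation techniques will be used to handle missing data in the main analysis"**.** The cost-effectiveness analysis is separate and may use its own missing-data method.

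**Conclusion.** The concern holds as a wrongly worded rule: as printed, it contradicts the MAR handling around it. It does not hold as a finding that the primary outcome will be mean-imputed.

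Applied literally with the plan's inputs and 13% random loss per arm, it would cost about 0.6 points of a 5-point effect, about 2 percentage points of coverage and about 4 points of power. Type I error would reach about 10% only under the assumed unequal, baseline-dependent dropout. Under the probable meaning there is essentially no bias, coverage is about 95%, and some precision is lost in proportion to how much baseline is missing.

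These sizes rest on normal scores and on a 12-week ANCOVA in place of the full MMRM. The sample size of 196 is reproduced and unaffected.

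**What to change.** Replace the imputation sentence in Statistical Analysis with:

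> Missing baseline values of the corresponding outcome, used as a covariate, will be replaced by the pooled baseline mean across arms; post-randomization outcomes, including fall counts, will not be mean-imputed, and the MMRM will use all observed 6- and 12-week data under MAR.

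Make the same statement in the SAP if it carries the present wording, and date the change before the analyst is unblinded. The cost is one sentence; no extra data are needed and the sample size does not change. The sentences on MAR and its sensitivity analyses can stay as they are.
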